## Abstract

**Background:**

Medically unexplained symptoms are an important mental health problem in primary care and generate a high cost in health services.

Cognitive behavioral therapy and psychodynamic therapy have proven effective in these patients. However, there are few studies on the effectiveness of psychosocial interventions by primary health care. The project aims to determine whether a cognitive-behavioral group intervention in patients with medically unexplained symptoms, is more effective than routine clinical practice to improve the quality of life measured by the SF-12 questionary at 12 month.

**Methods/design:**

This study involves a community based cluster randomized trial in primary healthcare centres in Madrid (Spain). The number of patients required is 242 (121 in each arm), all between 18 and 65 of age with medically unexplained symptoms that had seeked medical attention in primary care at least 10 times during the previous year. The main outcome variable is the quality of life measured by the SF-12 questionnaire on Mental Healthcare. Secondary outcome variables include number of consultations, number of drug (prescriptions) and number of days of sick leave together with other prognosis and descriptive variables. Main effectiveness will be analyzed by comparing the percentage of patients that improve at least 4 points on the SF-12 questionnaire between intervention and control groups at 12 months. All statistical tests will be performed with intention to treat. Logistic regression with random effects will be used to adjust for prognostic factors. Confounding factors or factors that might alter the effect recorded will be taken into account in this analysis.

**Discussion:**

This study aims to provide more insight to address medically unexplained symptoms, highly prevalent in primary care, from a quantitative methodology. It involves intervention group conducted by previously trained nursing staff to diminish the progression to the chronicity of the symptoms, improve quality of life, and reduce frequency of medical consultations.

**Trial registration:**

The trial was registered with ClinicalTrials.gov, number NCT01484223 [
http://ClinicalTrials.gov].

## **Background**

### **The somatoform disorders**

Somatic symptoms are those symptoms that cannot be medically explained and when they only have a somatic nature, they are referred to as somatoform disorders. They can be found in a healthy population as well as in patients with psychiatric disorders; and they represent an important reason for doctor’s examination in primary care. This group of disorders includes 
[1]: disorder caused by somatization (including 8 symptoms), syndrome by abbreviated somatization (4 symptoms throughout the whole life in men or 6 in women), or multi-somatoform disorder (three or more important symptoms without medical explanation and more than 2 years of development).

The diagnosis of these disorders is difficult. The classification of somatoform disorders in CIE-10 and in DSM IV is shown in Table 
1.

**Table 1 T1:** Somatoform disorders classification

	**International Classification of Diseases, 10th version (ICD-10)**		**Diagnostic and Statistical Manual of Mental Disorders, 4th Edition (DSM-IV)**
**F45**	**Somatoform disorders**		**Somatoform disorders**
F45.0	Somatization disorder	300.81	Somatization disorder
F45.1	Undifferentiated somatoform disorder	300.82	Undifferentiated somatoform disorder
F45.2	Hypochondriacal disorders	300.7	Hypochondriasis
F45.3	Somatoform autonomic dysfunction	300.7	Body Dysmorphic Disorder
.30	Heart and cardiovascular system		
.31	Upper gastrointestinal tract	307.8	Pain Disorder Associated with Psychological Features
.32	Lower gastrointestinal tract	300.11	Conversion Disorder
.34	Genitourinary system		
.38	Other organ or system		
F45.4	Persistent somatoform pain disorder		
F45.8	Other somatoform disorders		
F45.9	Somatoform disorder, unspecified		

Today, there is debate about the suitability of somatization disorder differ from other functional symptoms. It is estimated that 75 % of patients with medically unexplained symptoms (MUS) and over-the health system does not meet the diagnostic criteria for abbreviated somatization syndrome 
[2]. While somatization disorder affecting 0.4 % of the population, all somatoform disorders are between 20 and 30 % of consultations in primary care 
[2]. When the patient has at least one symptom in 5 specific areas (pain, fatigue, irritable bowel syndrome, somatic symptoms of anxiety or somatic symptoms of depression) and protracted (at least 4 consultations in a year) some authors recommend defining it as MUS 
[3]

In a clinical series in the USA, a clear organic cause was not found among the 20 % - 84 % of the patients that went to the family physician with throbs, thoracic pain, migraine, fatigue or sickness 
[4]. On the other hand, up to 75 % of the patients with major depressive disorders or anxiety attacks go to their family doctors only because of the somatic symptoms they show 
[5].

A study in Spain 
[6] shows that 34.5 % of patients who visit for the first time to their family physician suffer from for somatic symptoms. Most of these symptoms are severe, and a percentage end up having a somatization disorder or undifferentiated somatization disorder.

The somatoform disorders are an excluding diagnosis that forces to carry out a significant number of complementary tests and derivations to the second and third level.

The somatoform disorders are highly prevalent in primary care 
[2]. It is estimated that this kind of patient uses up 14 times more resources in outpatient, and 6 times more expenses under hospital regimen 
[7].

### **Approach to the somatoform disorders**

There is consensus that the approach to the different features of somatoform disorders should be carried out with similar interventions; without indicating specific therapies for each of the aforementioned manifestations 
[8].

There is data on the usefulness of the implementation of Good Clinical Practice (GCP) criteria (Table 
2), by the family physician; showing that they can relieve the symptoms, reduce the demand on attention, improve the patients’ satisfaction with the given attention and limit the costs; though with modest results 
[8]. It is important to find tools in the psychosocial approach of these patients added to those already recommended for GCP. The Cognitive Behavioral Therapy (CBT) or the psycho-dynamic psychotherapy has been useful in the field of secondary medical care 
[9-11]. In a recent systematic review of the 34 analyzed RCTs on interventions in somatoform symptoms, only 9 are developed in primary care 
[12]. In these nine RCTs conclude significant results in the decrease of use of services 
[13-16], improvement on physical and/or psychical performance 
[17-20]. The reattribution technique specifically designed by Goldberg and Cols 
[21] is used in two of the analyzed studies for the treatment of somatization in primary care through the teaching and training of family physicians. Their results show low improvement on the physical symptoms 
[22,23] but there is a significant decrease in the prescription of analgesic medication (8.1 %-23 %) and anti-depressants (11.3 %-26.9 %). The interventions carried out by nursing professionals are effective, but they are excessively expensive in terms of number of sessions (at least 12) and in the required training time (80 hours) 
[8].

**Table 2 T2:** Regulations on good clinical practice in the general approach of the patient with medical unexplained symptoms

	
1. To plan regular appointments every 4–6 weeks in order to treat them clinically during the first year / 6 months, or if a new symptom comes up (in worsening periods, appointments could be more frequent).	
2. To give the patient a detailed document on the origin of the symptoms	
3. To establish high-priority objectives	
4. To restrict complementary examinations to the most indispensable ones	
5. To control the visits to specialists	
6. To have the patient treated by only one doctor	
7. To calm down and to reassure	
8. To identify the psychosocial stimuli that are involved as well as their link to the worsening of the symptomatology	
9. To avoid ambiguous information about the findings that come up	
10. To avoid spurious diagnostics	
11. Not to treat what the patients do not suffer from	
12. To avoid dichotomy explanations, i.e. (mental-physical nature)	
13. To mediate, when possible, in their psychosocial problems	
14. The best policy is to be sincere on the reports	
15. To approach some problems in a multidisciplinary way	
16. To organize the management/treatment of the difficult cases	
17. To be consistent with the approaches	
18. To properly remit to the psychiatry services	

An alternative for the treatment of this kind of disorder in the field of primary care could be group interventions with a limited number of sessions. Martin A et al 
[24] carry out an RCT that assessed the effectiveness of a single cognitive-behavioral group session (relaxation and motivation technique to take physical exercise) in order to improve the approach of the patient to the symptoms, by means of their explanation from a non- biologist focus. They found a significant reduction in the seriousness of the symptoms, in the number of consultation to the family physicians (not in the visits to the specialist), reduction in number of drug (prescriptions) and in the number of days on sickness absence. This intervention was carried out by mental health professionals, which limits its external validity and its implementation in the field of primary care.

A correct approach to these patients by their family doctor may reduce iatrogenic. The training of primary care professionals can help to improve care for patients consulting for MUS.

A model on cognitive-behavioral group intervention, based on reattribution techniques, carried out through four group sessions by primary care nurses, together with the implementation of regulations on GCP, would be effective for improving quality of life of patients with MUS.

### **Aims**

The aim of the present work is to determine whether a cognitive-behavioral intervention group in patients between 18 and 65 years old with medically unexplained symptoms, is more effective than routine clinical practice to improve the quality of life measured by SF-12 questionnaire at one year follow-up.

The secondary objectives are to determine whether a cognitive-behavioral intervention group with medically unexplained symptoms, is more effective than routine clinical practice to:

– Improve the quality of life measured by SF-12 questionnaire at 3 and 6 months.

– Reduce the drug consumption.

– Reduce the number of medical consultation.

– Reduce the days of sickness absence.

– Raise the perception on improvement (standardized global vision) from the patient's point of view (PGI-I questionnaire) and from the doctor’s (with the CGI-I).

## **Methods/Design**

### **Design of the study**

This study is a community, parallel clinical trial, randomised by clusters, that compares cognitive-behavioral intervention group with routine clinical practice. The intervention will be carried out by health professionals in 14 Primary Health Care Centres (PHCCs), in Madrid (Spain).

The randomization units will be the PHCCs (clusters). The units of analysis will be the patients between 18 and 65 years old with MUS who have seeked medical attention in PHCCs at least 10 times over the past year. The design by clusters minimised possible contamination effects between centres.

### **Subjects of the study**

Adult patients between 18 and 65 years old with MUS, defined by the occurrence of two or more symptoms during the last 6 months without any evidence of organic disease that could explain them, and who have seeked medical attention in primary care at least 10 times during the last year.

1) *Inclusion criteria*. All patients were required to be:

a. Be able to meet the demands inherent to the trial, i.e, to have no intention of moving, to be reachable for the next year, and to have the capacity to understand the questionnaires presented

b. Give signed informed consent to be included in the study, and to meet no exclusion criterion.

2) *Exclusion criteria.*

a. Diagnosis of severe mental disorder.

b. Suicidal ideation at the time involved in the study.

c. Diagnosis of addiction to toxic substances.

d. Diagnosis of organic disease responsible for the symptoms.

e. Previous psychotherapy during the previous year.

#### ***Randomisation***

The randomization unit will be the PHCC. An independent statistician will randomly assign the 14 PHCCs (7 centres in each group) to either the intervention group or a control group following a simple, computer-generated random sequence (Epidat 3.1 software).

Consecutive patients will be chosen to minimize the risk of bias in their selection.

During consultations, patients will be informed about the study and asked whether they would like to take part. Those who accept will be asked to give their signed consent, and checks were made to ensure they met all inclusion criteria but no exclusion criteria.

#### ***Sample size***

##### *Method of calculation*

For an alpha of 0.05, a power of 80 %, and in order to detect an increase of 20 % in the proportion of patients that improve at least 4 points on area of mental healthcare of the SF-12 questionnaire (50 % in the intervention group and 30 % in the control group), the overall sample size required is 206 patients (103 in each arm of the study).

Since randomization is by clusters, the sample size had to be larger than if simple randomisation had been performed, in order to take into account the design effect. The intra-class correlation coefficient is 0.01 
[25,26] and a mean cluster size is assumed to be 8 patients. The design effect is 1.07. Given these assumptions, and expecting a 10 % loss rate at one year, the final sample size required is 242 (121 in each arm).

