### **Masking**

In a study of this type it is impossible to mask the intervention. The analysis data will be performed by independent professionals blinded to the assignment group.

Intervention:

a. In the control group:

Routine clinical practice: The clinical approach of the patients will be done following the recommendations of clinical practice guidelines as detailed in Table 
2.

b. In the intervention group:

Besides the routine clinical practice, four weekly cognitive-behavioral group sessions of 2 hours guided by nurse professionals will be carried out in the PHCC. The groups will be made up by 6–12 patients.

The content of the sessions will be as follows (Table 
3):

**Table 3 T3:** Structure of the group sessions in the intervention group

1.	COGNITIVE REATTRIBUTION
	· Psychological explanation of the symptoms: To explain the objective of the session that is not precisely to heal the symptoms, but rather “to improve doping". To explain that somatization is a common phenomenon resulting from different factors and mechanisms. The patients are asked to talk about the different factors; and stress is introduced as an explanatory element of the symptoms.
	· The importance of the cognitive issue. They give examples on the role of knowledge and the patients are asked to link them to their own experiences. The objective is to show how the behaviors and the attitude toward the symptoms could change the response to them.
2.	RELAXATION AND SYMPTOMATIC RELIEF
	· Once the role of stress in the genesis of pain has been described, techniques are introduced where physical exercising and muscular relaxation are combined. The patients are provided with a CD with spoken instructions.
3.	BEHAVIOR-ILLNESS
	· The patients are given details on optional treatments and on the correct use of sanitary services. They are also instructed on the mechanisms to control anomalous behavior toward the illness.
4.	AEROBIC EXERCISING
	· To encourage physical exercising: to do away with the bad habit of stating that “pain stops me from doing any kind activity” thus, they avoid doing any kind of activity. An ongoing program on physical exercising is outlined.

If the study results prove that the intervention is effective, cognitive behavioral sessions are planned for the patients in the control group.

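### The design effect uses 8 patients per cluster, but 242 patients in 14 randomised centres is about 17 per cluster, so 242 gives about 76% power, not 80%

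*Protocol article*

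**What the plan says.** Under Sample size (Method of calculation), the protocol article sets the error rates ("For an alpha of 0.05, a power of 80" %) and the target difference in the proportion improving by at least 4 points on the SF-12 mental health area ("50 % in the intervention group and 30 % in the control group"). Before allowing for clustering, "the overall sample size required is 206 patients (103 in each arm of the study"). It then inflates for cluster randomisation: "The intra-class correlation coefficient is 0.01", and "a mean cluster size is assumed to be 8 patients. The design effect is 1.07". After a 10% allowance for loss at one year, "the final sample size required is 242 (121 in each arm").

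The cluster is defined elsewhere. Design of the study makes the primary health care centre the unit of randomisation, and Randomisation fixes the number: "An independent statistician will randomly assign the 14 PHCCs (7 centres in each group"). A figure close to 8 appears only in the description of the intervention under Masking: "The groups will be made up by 6–12 patients". That refers to the therapy groups.

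**The concern.** The design effect must use the number of patients per randomised unit. Three of the article's figures cannot all be true: 14 centres, 8 patients per centre, and 242 patients. Nothing in the article reconciles them. The 8 may have been carried over from the size of a therapy group, but that is a guess. Therapy groups exist only in the intervention arm and are not what is randomised.

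The penalty for clustering grows with cluster size minus one. That is 16.3 for the real design against 7 for the stated one, more than double. The stated 1.07 therefore understates the variance inflation, overstates the power of 242 patients, and hides how sensitive the trial is to the intra-class correlation. A reader of a null result would credit the trial with power that it did not have.

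**Working it through.** **Inputs.** From Method of calculation: alpha 0.05 (taken as two-sided, which reproduces the article's figure), power 80%, proportions 0.50 and 0.30, intra-class correlation (ICC) 0.01, loss 10%, total 242. From Randomisation: 14 centres, 7 per arm.

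**Step 1: reproduce the article's figures.**
- Two-proportion formula without continuity correction, with mean proportion 0.40: n′ = [1.96·√(2·0.40·0.60) + 0.8416·√(0.25 + 0.21)]² / 0.20² = 93.0 per arm.
- With the Fleiss continuity correction: n = (n′/4)·[1 + √(1 + 4/(n′·0.20))]² = 102.8, rounded up to 103 per arm, or 206 in total. Of these two versions, only the corrected one gives the article's 206.
- Design effect for 8 per cluster: 1 + (8 − 1)·0.01 = 1.07.
- 206 × 1.07 = 220.4. Multiplying by 1.10 gives 242.5, the stated total. Dividing by 0.90, which is what leaves the required number after a 10% loss, gives 244.9.

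So each step follows from the one before it. The fault lies in one input, the cluster size, with a small further slip in how loss is applied.

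**Step 2: compare cluster size with the design.**
- 14 × 8 = 112 patients
- 242 / 8 = 30.25 centres
- 242 / 14 = 17.29 patients per centre

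**Step 3: design effect and requirement with the real cluster size.**
- At recruitment: 1 + 16.29 × 0.01 = 1.163.
- On analysed patients: 242 × 0.90 = 217.8, or 15.56 per centre, giving 1 + 14.56 × 0.01 = 1.146.
- Requirement: 206 × 1.163 = 239.6 before loss. This becomes 266 with /0.90, or 264 with ×1.10.
- Check that 266 is self-consistent: 266/14 = 19 recruited and 17.1 analysed per centre, a design effect of 1.161, and 206 × 1.161/0.90 = 266.

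**Step 4: power of 242 with 10% loss (108.9 analysed per arm, ICC 0.01).** Effective n per arm is 108.9 divided by the design effect. For the corrected power, the continuity correction is inverted as n′ = (n − 1/0.20)²/n and n′ is entered in the uncorrected formula. The last column uses a noncentral t with 14 − 2 = 12 degrees of freedom and noncentrality 0.20/√(0.46/n).

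| Patients per cluster | Design effect | Effective n per arm | Power, continuity-corrected | Power, uncorrected | Power, t on 12 df |
|---|---|---|---|---|---|
| 8 (as stated) | 1.070 | 101.8 | 79.6% | 83.5% | 78.0% |
| 15.56 (analysed) | 1.146 | 95.1 | 76.5% | 80.9% | 75.2% |
| 17.29 (recruited) | 1.163 | 93.6 | 75.8% | 80.3% | 74.5% |

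**Step 5: sensitivity to the ICC.** The article gives only 0.01; the values 0.02 and 0.05 are assumptions. With 15.56 analysed per centre, 0.02 gives a design effect of 1.291 and power of 71% corrected (76% uncorrected). An ICC of 0.05 gives 1.728 and 56% (63%). With 8 per centre the corrected figures would have been 77% and 69%.

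**The case against.** The inconsistency itself cannot be argued away. The case on the other side concerns its consequence.

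- **The formula.** Statistical Analysis names a chi-squared test and does not mention a continuity correction. Without one, 242 patients less 10% still give 80 to 81% power at the real cluster size, because 103 per arm already exceeds the uncorrected 93. This is correct and limits the size of the problem. It does not rescue the stated calculation, because 206 comes from the corrected formula and changing formula afterwards abandons it. The uncorrected figure also takes no account of there being only 14 clusters. The t test on 12 degrees of freedom is not an analysis the article plans; it serves here only as a check on that point.
- **The analysis set.** The article plans intention to treat with last observation carried forward, so all 242 could be analysed. That gives 121/1.163 = 104.1 effective patients per arm and about 80.5% corrected power. But the sample-size section itself budgets for a 10% loss, and a carried-forward value is not the same as an observed 12-month outcome.
- **Side points.** The loss factor moves the total only from 242 to 245, and the higher ICC values are assumptions that the article does not make. Both are fair limits, and neither is needed for the conclusion.

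**Conclusion.** The concern holds. The cluster size of 8 and the design effect of 1.07 do not describe a trial of 242 patients in 14 centres. At the article's own ICC the design effect is about 1.15 to 1.16.

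By the formula that yields 206, the requirement is about 266 rather than 242, and 242 with the planned loss gives 75.8 to 76.5% power against the stated 80%. The shortfall is about 4 percentage points. It rests on a two-sided alpha of 0.05, the continuity-corrected formula, centres of equal size, an ICC of 0.01 and a 10% loss of analysable patients. It vanishes if the continuity correction is dropped and the small number of clusters is ignored, and it widens if the ICC exceeds 0.01.

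The effect is modest, but the stated basis for the primary outcome's sample size contradicts the randomisation section and should be corrected.

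**What to change.** Rewrite the clustering part of the sample-size section around the actual design:

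- 14 centres, with about 17 patients recruited and 15.6 analysed per centre
- a design effect of 1.16 at recruitment (1.15 at analysis) for an ICC of 0.01
- the loss allowance applied by dividing by 0.90
- the power of 242 patients for 50% against 30% restated as about 75 to 76%, naming the formula used
- one line showing power for ICC values of 0.02 to 0.05, labelled as assumed

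This changes wording only. It needs no extra enrolment, and its cost is a slightly less favourable power statement. If the claim of 80% is to be kept, the matching total on 14 centres is about 266 patients (19 per centre). If a cluster size of 8 was really intended, 242 patients would need about 30 centres, and the number of randomised centres would have to change to match.

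### The 10 % loss allowance appears to have been added as × 1.10 instead of ÷ 0.90, so 242 patients fall slightly short of the plan's own target after loss (a minor slip)

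*Protocol article*

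**What the plan says.** The calculation is in the Protocol article under Sample size, Method of calculation. It starts "For an alpha of 0.05, a power of 80" per cent, assumes response proportions of "50 % in the intervention group and 30 % in the control group", and concludes that "the overall sample size required is 206 patients (103 in each arm of the study").

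It then allows for clustering. "The intra-class correlation coefficient is 0.01", "a mean cluster size is assumed to be 8 patients", and "The design effect is 1.07". After a further allowance for a 10 % loss at one year it states that "the final sample size required is 242 (121 in each arm"). The Abstract repeats the result: "The number of patients required is 242 (121 in each arm").

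The section prints neither the intermediate total after the design effect nor the formula used for the loss. It also does not name the two-proportion formula behind 103 per arm.

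**The concern.** A loss rate is a share of the patients enrolled. If 10 % are lost, 90 % remain, so the number to enrol is the number needed at the end divided by 0.90. Multiplying by 1.10 gives a smaller number, because 1.10 × 0.90 = 0.99: about 1 % of the target is missing once the loss has occurred.

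The stated 242 matches the multiplication and not the division. At stake is whether the figure that the article calls required delivers the number that its own inputs call for.

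**Working it through.** **Inputs, all from Method of calculation:** alpha 0.05; power 80 %; 50 % v 30 %; 103 per arm (206); ICC 0.01; mean cluster size 8; design effect 1.07; loss 10 %; final size 242 (121 per arm). Two-sided testing is assumed because the article does not state sidedness; it reproduces 103, whereas one-sided testing gives 74 (uncorrected) or 83 (corrected).

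**1. Base size.**
- Uncorrected: n = [1.96 √(2 × 0.4 × 0.6) + 0.842 √(0.5 × 0.5 + 0.3 × 0.7)]² / 0.2² = 93.0, so 93 per arm.
- With continuity correction: (n/4) × [1 + √(1 + 4/(n × 0.2))]² = 102.8, so 103 per arm, 206 in total. The plan's figure is reproduced, and only with the correction.

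**2. Design effect.** 1 + (8 − 1) × 0.01 = 1.07, as stated. 206 × 1.07 = 220.4 in total, or 110.2 per arm.

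**3. Loss allowance, two ways.**

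| Step | Total | Per arm |
|---|---|---|
| 220.4 × 1.10 | 242.5 | 121.2 |
| 220 × 1.10 | 242.0 | 121.0 |
| 220.4 ÷ 0.90 | 244.9 | 122.5 |

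The multiplication returns 242 and 121. The division gives 245, or 246 (123 per arm) with equal arms.

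**4. What 242 leaves.**
- 242 × 0.90 = 217.8, against 220.4: 2.6 too few.
- Using printed numbers only: 217.8 / 1.07 = 203.6, below the stated 206. This step does not depend on how 242 was reached.
- Loss that 242 can absorb: 1 − 220.4/242 = 8.9 %, or 1 − 220/242 = 9.1 % if the target is taken as 220. Either way, about 9 %.

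**5. Power at 10 % loss.** The effective size is 121 × 0.90 / 1.07 = 101.8 per arm, against 103. Power = Φ[(0.2 − c − 1.96 √(0.48/n)) / √(0.46/n)], with c = 1/n for the continuity correction and c = 0 without it.

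| | n = 103 | n = 101.8 |
|---|---|---|
| Continuity-corrected | 80.1 % | 79.6 % |
| Uncorrected | 83.9 % | 83.5 % |

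**The case against.** **The power target may not be missed at all.** A reader might infer that the trial fails its stated 80 %. The documents do not support that as a general statement. Statistical Analysis names a Chi-squared test and mentions no continuity correction. For an uncorrected test 93 per arm suffice, so 186 × 1.07 / 0.90 = 221 patients would be enough and 242 gives 83.5 % after loss. Power falls below 80 % only under the corrected formula, which is itself inferred from the match to 103. This objection stands against any claim of missed power. It does not make the printed figures agree.

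**Lost patients stay in the analysis.** Statistical Analysis prescribes intention to treat with last observation carried forward, and Withdrawal keeps the data of withdrawn patients. The number analysed may therefore exceed 217.8. But the plan itself chose to enlarge the sample for loss, and carrying a value forward does not restore the missing month-12 information. The allowance should be right on its own terms.

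**The gap is within the slack of the inputs.** If 8 is the cluster size at recruitment, 7.2 remain after loss and the design effect becomes 1 + 6.2 × 0.01 = 1.062. The need is then 206 × 1.062 = 218.8, one patient more than 217.8, with power 79.9 % even with the correction. The article does not say whether 8 is before or after loss. The response proportions and the ICC are also less certain than a difference of 1 to 2 %. This stands, and it is why the point is minor.

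**The × 1.10 step is inferred.** True; so is the intermediate 220. The inference explains the cause, while the mismatch in step 4 uses printed numbers alone.

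**Conclusion.** The point holds as a small arithmetic slip. On the plan's own inputs, 242 patients leave 217.8 after a 10 % loss where 220.4 are needed. The correct divisor adds 3 to 4 patients (245, or 246 with equal arms), and the cost in power is about 0.5 percentage points: 80.1 % to 79.6 % corrected, 83.9 % to 83.5 % uncorrected. It does not show a materially underpowered trial.

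All these figures take the design effect of 1.07 as given. Whether it fits the design is a separate question: 242 patients in the 14 centres named under Randomisation is 242/14 = 17.3 per centre, not 8. Thus 246 should not be read as the right sample size for this trial, only as the result of the plan's inputs with the loss step corrected.

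**What to change.** Change one sentence under Method of calculation; no further patients need be enrolled. Either of these suffices:

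- state that 242 patients meet the target of about 220 for losses up to about 9 %; or
- state that at a 10 % loss the power is about 79.6 %, for the continuity-corrected formula and a design effect of 1.07.

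Name the two-proportion formula in the same sentence, so that a reader can tell which power figure applies. If the calculation is redone, for example when the assumed cluster size of 8 is reconciled with 242 patients in 14 centres, divide by (1 − loss). If the total changes as a result, the Abstract must follow. The cost is editorial.
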